### Treatments

#### Group schema therapy

Schemas refer to the knowledge representations people have about themselves, others and the world and which are formed during childhood by the way basic needs are met. When a child has to cope with his or her basic needs not being met, a variety of dysfunctional schemas, and/or coping styles, may develop. Schema modes refer to the emotional states between which BPD patients can rapidly switch when triggered by events that are related to the unmet needs during childhood. Schema modes represent sets of schemas and/or coping styles that are typically expressed in such emotional states. The following schema modes are characteristic for BPD: the vulnerable (abandoned/abused) child, angry/impulsive child, punitive parent, detached protector (or any other protective mode), healthy adult and happy or contented child. The first four of these modes are maladaptive and strongly present in BPD patients. The latter two are functional modes and weak in BPD patients. Schema therapy aims to reduce maladaptive modes and develop and strengthen functional modes [29]. This schema mode model guides therapy as each mode requires a different treatment strategy. The strategies comprise specific experiential, cognitive and behavioural techniques [30]. When offered in a group format, several factors may amplify and speed up recovery: peer support, a sense of belonging and understanding, opportunities for vicarious learning and real-life practice of healthy behaviour [19].

In format A (GST-A), two-year GST consists of 124 groups sessions with a duration of 90 minutes. In the first year group sessions take place twice a week and in the second year the frequency gradually decreases. In addition, in GST-A a total of up to 18 individual sessions can be used at the patients discretion or in times of crisis. Two individual sessions take place before group sessions commence. At this time patients get acquainted with their group schema therapists, schema therapy and the schema mode model are explained, the schema modes a patient has and their relationship to one another are identified and a treatment plan is drawn up.

In format B (GST-B), two-year GST involves a combination of group and individual sessions. In the first year, there are weekly group sessions of 90 minutes and individual sessions of 50 minutes and in the second year the frequency gradually decreases. In total, patients in this condition receive 74 group sessions and 62 individual sessions. In the first two individual sessions patients get acquainted with their individual and group therapists, schema therapy and the schema mode model are explained, the schema modes a patient has and their relationship to one another are identified and a treatment plan is drawn up. Group and individual ST therapists meet regularly to coordinate treatments.

#### Treatment as usual

Following usual procedures, the intake staff at each centre determine the optimal treatment offered to each patient in the TAU condition. Except for (G)ST, the intake staff are allowed a choice from the whole array of possible treatments for BPD with no restriction; whether intensive, individual, group, inpatient, outpatient or day treatment. The TAU condition is thus representative of optimal current practice and will be carefully monitored for all patients. Since there is no protocol for TAU in this RCT and specific treatment is decided on by experts in the community treatment centre, TAU is equivalent to ‘community treatment by experts’.

In some centres, the treatment that is usually offered to BPD patients is Dialectical Behavioural Therapy (DBT). This is an empirically validated treatment for BPD [24,31]. If the number of centres that offer DBT as the usual treatment is sufficient, this will provide an opportunity to compare the clinical effectiveness and cost-effectiveness of GST with DBT.

### Therapists, training and supervision

GST sessions are run by two schema therapists, of whom at least one is a senior schema-therapist. Stand-in schema therapists replace the regular therapists when they are absent (e.g. due to illness, holidays or pregnancy). The senior therapist’s role, in addition to being a group schema therapist, is to act as a local supervisor for other schema therapists. Individual schema therapists can also be group schema therapists for GST. Group schema therapists receive a training of six days in GST [32]. Candidate ST therapists (individual and group) who are not yet trained in ST first receive a 3–4 day training in individual ST for BPD [33]. During the study intensive supervision meetings are held twice a year in the first year and once or twice a year in the second year. In addition, weekly team supervision is provided locally and central supervision by the developers of GST is provided through teleconferencing and viewing of video-recordings weekly in the first months, then biweekly and monthly after about 6 months. Initially, a computer program was acquired that was especially designed to enable secure online sharing of video-recordings of medical procedures through encrypted streaming. Unfortunately, this program has become unavailable. The encrypted recordings will now be uploaded on a central server so that supervisors can download and watch them.

## Evaluation of clinical effectiveness

In this section, the primary and secondary clinical outcome measures that will be used to evaluate the clinical effectiveness of the treatments are described as well as the strategy used for analysis of the data. All instruments that will be used to investigate clinical effectiveness that were not yet available in the languages of all participating sites were translated. Translated versions were back-translated and thoroughly checked for consistency with the original version. Any inconsistencies were addressed in consensus meetings and adjusted accordingly. Instruments are implemented in an online data collection environment.

### Clinical outcome measures

#### Borderline Personality Disorder Severity Index version IV (BPDSI-IV)

The primary outcome measure is the severity of BPD, expressed as a score between 0 and 90 as measured with the Borderline Personality Disorder Severity Index (BPDSI), version IV. The BPDSI-IV is a semi-structured interview containing 70 items based on the nine BPD dimensions described in DSM-IV. This is a reliable and valid instrument, suitable for use as an outcome measure [21,34]. A cut-off score of 15 between patients and controls has been previously established [21,34]. Therefore, a score below 15 measured two years after randomization or earlier and maintained until follow-up can be used as a criterion for recovery. The scores on subscales of the BPDSI-IV provide information on the severity of each of the nine dimensions of BPD. The recall period for the BPDSI-IV is three months.

#### BPD checklist

The BPD checklist is a self-report instrument that measures the burden of BPD manifestations as experienced by patients. Since the BPD checklist measures changes in subjective burden, it is complementary to the BPDSI-IV that measures changes in symptomatology objectively. It consists of 47 items based on the nine dimensions of BPD in DSM-IV and answers are scored on a five point Likert scale. Suitability for use as a treatment outcome measure has been established [35]. The recall period for the BPD checklist is one month.

#### Brief Symptom Inventory (BSI)

The BSI is a self-report instrument used as an inventory of general psychiatric symptoms present at the time of assessment and is a short alternative to the SCL-90-R, from which it was developed [36]. It contains 53 items to inventory the following nine types of primary symptom dimensions: somatic, cognitive, inter-personal sensitivity, depressive mood, anxiety, hostility, phobia, paranoia and psychoticism. Answers are scored on a 5-point Likert Scale. Cronbach’s α is .96 for the instrument in total and ranges between .71 and .87 for its subscales [37]. According to [38], Cronbach’s α values of 0.9 or higher indicate an internal consistency that is appropriate for clinical applications, and values of 0.7 to 0.8 are satisfactory for comparing groups. In addition, the BSI has good discriminant validity [37].

#### Happiness item

The happiness item is a single question on general happiness in the months prior to the assessment and is scored on a seven point Likert scale [39]. This scale consists of the following verbal descriptions of different states of happiness: (1) completely unhappy, (2) very unhappy, (3) fairly unhappy, (4) neither happy nor unhappy, (5) fairly happy, (6) very happy, (7) completely happy. Norms for all participating countries are available [39]. For a single happiness item high test-retest reliability (r = 0.86) and good concurrent, convergent, and divergent validity have been reported [40]. The happiness item has excellent sensitivity to change for patients with BPD who were treated with GST [20].

#### Schema Mode Inventory (SMI)

The SMI is a self-report instrument that consists of 143 items on 16 schema modes that are scored on a six point Likert scale. It measures the extent to which dysfunctional as well as functional schema modes are present at the time of assessment [41]. It is an adaptation of the original SMI containing 270 items [42] and short SMI containing 118 items [43]. This instrument is only used for patients in the GST condition. Its subscales have satisfactory to high internal consistency (Cronbach’s α ranges from .79 to .96) [43]. The SMI is a useful instrument for assessing modes in ST [43].

#### Young Schema Questionnaire – short form (YSQ)

The YSQ is a self-report instrument containing 75 items that are scored on a six point Likert scale [44]. It is used to measure the presence or absence of 16 core maladaptive schemas at the time of assessment. The YSQ has adequate temporal as well as rank-order stability and an analysis of its discriminant power in clinical versus non-clinical samples revealed it is highly sensitive in predicting the presence or absence of psychopathology [45]. Internal consistency is high for the overall scale (Cronbach’s α ranges from .94 to .96) and satisfactory to high for its subscales (Cronbach’s α ranges from .72 to .94) [46].

#### Global Assessment of Functioning (GAF) and Social and Occupational Functioning Assessment Scale (SOFAS)

Based on axis V of DSM-IV, the GAF and SOFAS are 100-point scales used to assess general and social/occupational functioning, respectively. A short semi-structured interview serves to elicit the information needed for scoring. The recall period for both instruments is one month. The GAF is a valid scale of global psychopathology and the SOFAS is a valid measure of social, occupational and interpersonal functioning [47]. Both instruments have excellent interrater reliability (intraclass correlation coefficients > .74) [47].

#### Work and Social Adjustment Scale (WSAS)

The WSAS is a self-report instrument that consists of 5 items that are scored on a scale ranging from 0 to 8. It is used to assess functional impairment at the time of assessment in the domains of work, household, social leisure, private leisure and family and relationships. The WSAS’ reliability, validity and sensitivity to change have been firmly established in samples of patients with different clinical disorders [48-50].

#### Relationship Scales Questionnaire (RSQ)

The RSQ was designed as a continuous measure of adult attachment and consists of 30 short statements about romantic relationships [51,52]. After being instructed to think about such relationships in their past and present lives patients rate the extent that these statements resemble their own feelings and experiences at the time of assessment on a five point Likert scale. Scores are calculated for the following attachment patterns: secure, dismissive, fearful and preoccupied.

#### Emotional Core Needs Inventory (ECNI)

The ECNI is a list of 88 statements used to measure the extent to which basic needs are being met in important relationships at the time of assessment [53]. Each statement is rated on a scale ranging from 1 to 6. A higher rating corresponds to better need-fulfilment. Assessing the extent to which patient’s needs are met by others is important given that maladaptive schemas are hypothesised to result from unmet core emotional needs. A central aim of ST is to bring about changes that lead to better need-fulfilment of patients [54].

#### World Health Organization Quality of Life questionnaire (WHOQOL-short)

The WHOQOL-short is a self-report instrument for assessing quality of life in the two weeks prior to assessment. It is a short version (35 items) of the WHOQOL and focuses on the domains of physical health, psychological health, social relationships, environment, positive feelings, negative feelings and self-esteem. The WHOQOL-short is a reliable and valid instrument [55].

### Analyses

All available data on clinical outcomes will be analysed according to the intention-to-treat principle. Outcome measures will be analysed with mixed regression, also known as multilevel or hierarchical regression, with centre as a random effect, allowing centre by treatment interaction, and including patient-level and treatment indicator covariates, as well as time and treatment by time effects. Baseline covariates will be used to adjust for potential differences at baseline and to reduce standard errors. For categorical outcome variables, counts and in case of non-normal residuals, appropriate forms of mixed regression will be chosen (binomial, Poisson, gamma, etc.).

## Economic evaluation

The following section describes how costs and utilities will be measured for the economic evaluation as well as the planned cost-effectiveness and cost-utility analyses. The cost interview has been translated into the languages of all participating sites. The original Dutch version was first translated to English and subsequently this English version was then translated into Greek and German. The translated versions have been back-translated and/or thoroughly checked for consistency with the original version. Any inconsistencies were addressed in consensus meetings and adjusted accordingly. The cost interview will be implemented in an online data collection environment.

### Costs measurement

Costs will be measured from a societal perspective using a retrospective cost interview especially designed for BPD patients. Relevant costs to be identified include healthcare, patient and family costs, and costs outside the health care sector. Healthcare costs include visits to general practitioners, hospitals, psychiatrists and psychologists, crisis centres, use of medication, social work, formal care, and alternative treatments. Patient and family costs include travelling costs, informal care (care provided by family, friends or neighbours of the patient) and out of pocket costs (alcohol, drugs, smoking and self-reported other costs). Costs in other sectors include productivity losses from unpaid work (voluntary work and study) and paid work. The cost interview will be conducted by trained local research assistants, who will ask questions on the consumption of different resources and assess volumes of resource use. When applicable, calculations and descriptive content will be noted. For the cost interview the recall period is 6 months.

### Utility measures

#### EuroQol-5D-3 L (EQ-5D-3 L)

The EQ-5D-3 L is a generic, self-assessment instrument used for measuring health-related quality of life at the time of assessment [56]. It consists of five questions, each related to a specific dimension of health status: mobility, self-care, usual activity, pain/discomfort and anxiety/depression. The EQ-5D has been translated in the languages of all participating sites [57]. The descriptive profiles, generated by the EQ-5D-3 L are valued using social tariffs for the EuroQol to generate utilities, which reflect a population’s preference for a particular health profile.

In base-case analysis, country-specific tariffs will be used for valuation when available. For the Netherlands, Germany and the UK national tariffs are available, whereas for Greece and Australia they are not [57]. For these countries, proxy tariffs will be used as an alternative (e.g. tariffs for Europe and New-Zealand, respectively). Sensitivity analyses will be performed that make use of country-specific tariffs for the valuation of health profiles of all patients.

Utilities will be used to calculate Quality Adjusted Life Years (QALYs) by multiplying change in utility between assessments by the duration of the time period between assessments. Through the use of statistical regression, potential baseline differences in QALYs can be adjusted for [58].

In addition, the EuroQol thermometer will be scored in a range between 0 and 100 to provide a single index measure for a patient’s health status [56].

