### Assessments

Prior to randomization, patients will be assessed at baseline. Baseline assessments will be spread over a period of approximately three months on average. Once a cohort is nearly complete, baseline assessments can be speeded up so they are completed within a minimum time period of one month. Inversely, when inclusion is too slow, the maximum time period patients are required to wait before treatment will start is limited to one year. When baseline assessments are complete for all patients, patients will be randomized and treatment will start. Subsequently, patients will be re-assessed approximately every six months over the course of two years. Since the treatment duration for GST is also two years, the fourth assessment after baseline will coincide with GST treatment ending. Follow-up assessments will take place one year later. For the cost interview, a recall period of a year is considered too long. Therefore, an additional assessment will take place midway during the follow-up time period (i.e. two-and-a-half years after start of treatment) during which only the cost interview will be performed.

All assessments will be performed by local research assistants in the centres, except for SCID-interviews which will be done by trained interviewers blind for condition. Assessments include PC-based self-report questionnaires and interviews. An overview of the instruments used per assessment is provided in Table 1.

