### Analyses

The economic evaluation will be comprised of both a cost-effectiveness analysis (CEA) and cost-utility analysis (CUA) and will be performed from a societal perspective. All available data on costs and outcomes will be analysed according to the intention-to-treat principle. Data gathered with the cost interview will first be checked for adherence to questionnaire routing, illogical answers, unrealistic cost estimates and outliers. For any problems in the data that cannot be solved through logic, decision rules will be established. A decision rule could apply a specific limit to volumes of costs, e.g. the maximal hours patients spend per day on caring for their children can be limited to eight for patients who report doing this for 24 hours per day. For intermittent missing values at the item level of the cost interview the mean values of previous and subsequent assessments will be imputed to allow calculation of total costs. Missing values on total scores or other outcomes will not be imputed. Unrealistic or extreme values will be investigated per case and corrected when appropriate. Volumes of resource use as measured by the cost interview will be multiplied by their corresponding unit costs and then summed to provide an overall total cost. Unit costs will be based on standard unit prices for each country (e.g. in the Netherlands: Hakkaart-van Roijen et al. [59] for cost prices of healthcare services [59]) when available and on (averaged) tariffs otherwise. Cost prices will be expressed in Euros for the same base year and indexed using consumer price indices when required. Cost prices expressed in currencies other than Euros will be converted using purchasing power parities. In addition, to account for the three year time horizon of this RCT, cost prices will be discounted according to the guidelines. When neither standard unit prices nor tariffs are available for specific resource items in specific countries, alternative strategies for the valuation of resource use will be considered. When for a subset of resource items the unit costs are known in all countries and for all other resource items there is a unit cost available in at least one country, the unit cost of a resource item that is not available in one or more countries can be estimated through a procedure called market-basket based imputation [60]. In base-case analysis, country-specific unit costs will be used to value resource use for each country. Sensitivity of the results to differences in unit prices between countries will be analysed by valuing resource use in all countries using unit prices of a single country. Productivity losses will be valued by the human capital approach through multiplication of the total number of hours lost with the national average hour wage. Shadow prices will be used to value informal care and lost productivity in study and voluntary work. The primary clinical outcome for the CEA will be the BPD Severity Index (BPDSI) score and for the CUA primary utility scores will be derived from the EuroQol-5D. Cost-effectiveness and cost-utility data will be analysed with multilevel modelling techniques. The net monetary benefit will be used to express cost-effectiveness, and results will be expressed in cost-effectiveness acceptability curves. Net monetary benefit (NMB) will be calculated for a range of values for the amount decision makers are willing to pay (WTP) for an additional unit of effect, following: NMB = ∆E*WTP- ∆C, where ∆E is the difference in effects and ∆C is the difference in costs [61]. To accommodate the skewness that is typically observed in cost data, costs (or NMB) can be assumed to follow a gamma or log-normal distribution. Baseline covariates will be used to adjust for potential differences at baseline and to reduce standard errors. Results will be expressed in cost-effectiveness acceptability curves that display the probability, based on the available evidence, that GST can be considered cost-effective for a range of WTP values. For these types of analyses, a Bayesian approach is the most natural, since it allows direct and intuitive statements to be made regarding the probability that a treatment is cost-effective, based on the available evidence [62]. Furthermore, Bayesian methods allow flexible joint modelling of costs and effects, thereby facilitating sensitivity analyses regarding different methodological approaches for specification and parameterization of the model. Sensitivity analyses will be performed to address uncertainty regarding methodology, model specification and prior distributions.

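### The stated QALY rule multiplies the change in utility by the interval length; applied as written it is not a QALY and discards the timing of any gain within the two-year treatment period

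*Protocol article*

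**What the plan says.** The EuroQol-5D-3 L section describes the EQ-5D-3L as a "self-assessment instrument used for measuring health-related quality of life at the time of assessment", so each visit yields a utility level. The same section then says how utilities become QALYs: by "multiplying change in utility between assessments by the duration of the time period between assessments". The next sentence adds: "Through the use of statistical regression, potential baseline differences in QALYs can be adjusted for".

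On timing, the Assessments section says that "patients will be re-assessed approximately every six months over the course of two years", with follow-up one year later and a mid-follow-up visit for the cost interview only. Table 1 agrees: EQ-5D at baseline and 6, 12, 18, 24 and 36 months, none at 30 months.

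The Analyses part of the economic evaluation takes the cost-utility effect from the EuroQol-5D. It puts the difference in effects into NMB = ∆E × WTP − ∆C and reports acceptability curves. No other section gives an area-under-the-curve or mean-utility rule.

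**The concern.** QALYs are utility multiplied by time: over an interval, the average utility times the interval's length. The stated rule uses the difference between the two utilities instead. It is not the QALY gain within the interval either, since with linear change that gain is half the change times the length.

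Summing changes over equal intervals makes the intermediate values cancel. When a gain occurs during treatment, and how long it has been held by month 24, would then have no influence on the effect measure. That matters in this trial because the Abstract and Background put forward faster recovery as a possible advantage of group schema therapy (GST). Cost-effectiveness is part of the main objective, and any error in ∆E is multiplied by the willingness to pay.

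**Working it through.** **Inputs.** Assessment times t = 0, 0.5, 1, 1.5, 2 and 3 years (Assessments; Table 1). The article gives no utility values, so the utilities below (0.50 and 0.70) are assumptions for illustration. It also states no QALY figure, so there is none to reproduce.

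**Rule as written.** Sum over intervals of (u_j+1 − u_j) × (t_j+1 − t_j). The first four intervals are each 0.5 year and the last is 1 year, so

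0.5 × [(u6 − u0) + (u12 − u6) + (u18 − u12) + (u24 − u18)] + 1 × (u36 − u24) = 0.5 × (u24 − u0) + 1 × (u36 − u24).

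The utilities at 6, 12 and 18 months drop out.

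**Area under the curve.** Sum over intervals of (u_j + u_j+1)/2 × (t_j+1 − t_j). Gain is measured against a constant 0.50, which is worth 3 × 0.50 = 1.50 over three years.

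**Worked example: gain by month 6 and kept** (0.50, then 0.70 throughout).
- Area: 0.5 × 0.60 + 2.5 × 0.70 = 0.30 + 1.75 = 2.05; gain 2.05 − 1.50 = 0.55.
- Rule: 0.5 × 0.20 + 1 × 0 = 0.10.

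| Assumed profile | Area total | Area gain | Rule as written |
|---|---|---|---|
| 0.70 from month 6, kept | 2.05 | 0.55 | 0.10 |
| Linear rise to 0.70 at month 24, kept | 1.90 | 0.40 | 0.10 |
| 0.70 first at month 24, kept | 1.75 | 0.25 | 0.10 |
| 0.70 at months 6–18, back to 0.50 from month 24 | 1.80 | 0.30 | 0 |
| 0.70 only at month 36 | 1.60 | 0.10 | 0.20 |
| 0.70 at months 6–24, back to 0.50 at month 36 | 1.95 | 0.45 | −0.10 |

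The last row by the rule: 0.5 × 0.20 + 1 × (−0.20) = −0.10. By area: 0.5 × 0.60 + 1.5 × 0.70 + 1 × 0.60 = 1.95, less 1.50 = 0.45.

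**Between-arm differences.** The error is not a constant that cancels between arms.
- One arm gains by month 6, the other at month 24, both kept: area 0.55 − 0.25 = +0.30; rule 0.10 − 0.10 = 0.
- One arm gains by month 6 and keeps it, the other gains only at month 36: area 0.55 − 0.10 = +0.45; rule 0.10 − 0.20 = −0.10.
- One arm gains at months 6–24 and loses it by month 36, the other does not change: area +0.45; rule −0.10.

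In the first comparison the net monetary benefit is understated by 0.30 × WTP, whatever value of WTP is used.

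**The case against.** The strongest reply is that this is one sentence in a condensed article. It names the quantity as QALYs and may be loose wording for utility times time, or for QALY gain over baseline. That stands as a limit on certainty: a reader might infer that the analysis will certainly use a wrong measure, but the document supports only the conditional claim. It does not remove the point. The sentence is the only QALY rule given, an analyst following it would compute the wrong quantity, and a gain-over-baseline reading would still need the average change from baseline over each interval.

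Baseline regression does not repair it either, because a baseline covariate cannot bring back follow-up utilities that have already cancelled.

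Several stronger readings are tempting but not supported:
- *Early gains always score below late ones.* Gains first seen at month 6, 12, 18 or 24 and then kept all score 0.10. An early gain scores lower only against one that first appears after month 24.
- *The GST–TAU conclusion would generally reverse.* Reversal needs particular assumed profiles. Under steady improvement the sign is kept and the size shrinks (0.40 to 0.10).
- *Constant utilities of 0.9 and 0.5 both scoring 0 (area 2.70 and 1.50) shows a biased treatment contrast.* It shows mislabelling. A stable difference present at baseline is largely what baseline adjustment would remove.
- *Months 24–36 get an undue double weight.* That interval is twice as long and has the same width under the area rule.
- *Pre-randomisation time is counted.* The article does say that "the maximum time period patients are required to wait before treatment will start is limited to one year", but this is a maximum for slow inclusion. Nothing says that QALY time starts at the baseline visit, and Figure 1's legend times follow-up from randomisation.
- *"potential baseline differences in QALYs can be adjusted for" is an error because only utility exists at baseline.* This is a matter of wording; the economic Analyses section also provides for baseline covariates.
- *QALYs will go undiscounted because "cost prices will be discounted according to the guidelines" mentions costs alone.* Silence on QALY discounting in a condensed article does not establish that.

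**Conclusion.** The point holds in conditional form. The stated rule does not define a QALY, and nothing in the article corrects it. If followed as written, it loses all information on when a gain arose within the two-year treatment period. On the assumed utilities, a gain reached by month 6 and kept counts 0.10 instead of 0.55, and a 0.30 QALY advantage of early over month-24 gain becomes zero. The usual effect is an error of size. The sign changes only for some profiles, such as a gain held through month 24 and lost by month 36 (+0.45 against −0.10).

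The cancellation follows from the schedule alone; the numerical sizes rest on the assumed 0.50 and 0.70. The consequence is limited to the cost-utility analysis. The BPDSI-IV primary outcome, the BPDSI-based cost-effectiveness analysis and the sample size are unaffected.

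**What to change.** Replace the sentence with an explicit area rule: QALYs = sum over intervals of (u_j + u_j+1)/2 × (t_j+1 − t_j), with time in years, from randomisation to 36 months, over the intervals 0–6, 6–12, 12–18, 18–24 and 24–36 months. State that baseline utility enters the regression as a covariate, in place of the reference to baseline differences in QALYs. If area under the curve was always intended, this only clarifies the text.

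The cost is one or two sentences before analysis. No assessment, data collection or sample size changes.
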